### Study design

Case study pre-post test intervention in three electoral Ward areas of similar socio-economic deprivation [14] in a deprived inner city in the UK with an estimated population of ~10,000 adults.

Targeted communities in these wards will take part in an intensive community-led project, designed to engage its residents in the development and delivery of a range of health related interventions over a period of 2 years. The intervention will:

1. use community participatory research to build an effective community partnership in order to engage community residents, and strengthen community involvement and participation

2. use partnership consensus to identify, prioritise and design intervention(s) related to specific health disparities (and their relevant environmental determinants and mediators)

3. recruit local residents and Third Sector organisations to help with the delivery and sustainability of the target intervention(s)

4. establish local systems for ongoing monitoring and evaluation of the intervention

5. establish a local Public Health Advisory Group comprised of members from cross-government departments (e.g. urban planning, architecture, health, police and transport) to help facilitate policy change

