### Proposed sample size

Sample size calculations for the independent survey sample are based on Cohen's arcsine transformation for estimating differences between proportions [15], where;

$$\begin{array}{c} \varphi =2\;\text{arcsine}\left(\sqrt{\text{p}}\right)\\ \text{h}=\left|\varphi_{1}-\varphi_{2}\right| \end{array}$$

P is the proportion and h is the effect size to be detected. The best available estimate of the population proportion currently active at the recommended level was that taken from Active People Survey 2 [16] (sub-group NS-SEC 6-8 i.e. those most closely matching the demographic profile of the target population for this study), which was 7.5%. Based on our previous research [17], we anticipate being able to achieve a 10% increase in this population proportion i.e. 17.5% after the community-led intervention. Using Cohen's arcsine formula this gives a standardised effect size of 0.273. Assuming a false positive error rate of .05, statistical power of .8 and this standardised effect size, we have calculated a required sample size of 283 participants at follow-up. Further, assuming a survey response rate of 10% (expected to be low for this target population) the issued sample size will be 2830 surveys.

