### Community survey

Addresses will be selected from the postcode address file representing all of the targeted streets within each ward included in the study. Postal questionnaires will be sent to a random sample of addresses within the study area for each of the Lower Super Output Areas (LSOA). For each household a random date will be generated and the adult whose birthday falls closest to this date will be asked to complete the questionnaire (intended to select persons within the household with equal probability).

As an incentive, all participants will be entered in to a prize draw for £200 of High Street vouchers if they complete and return the questionnaire.

All respondents at wave 1 would be issued again at wave 2 (at 24 month follow up). This gives sufficient power to detect the expected 10% difference in population proportions. Since only one person is being randomly selected at addresses which have more than one resident aged 16+, at the analysis stage we would apply weights (equal to the inverse probability of selection) to adjust for this.

The self-report questionnaire will include validated and reliable questions on physical activity [21], behavioural intentions and behavioural change [22], perceived health - SF12 [23], perceptions of the local neighbourhood for physical activity (Neighborhood Environment Walkability Scale) [24], social capital [25] and socio-demographic information (gender, age, ethnicity, education level, household tenure). The questionnaire and survey procedures will be fully piloted before the main fieldwork for wave 1 and for any changes or additional questions at wave 2 (at follow up).

In addition to the survey a random sub-sample of 100 adults from each of the three Wards will be asked to wear an accelerometer (GMT1) for 7 consecutive days to measure physical activity levels [26].

Results from the objective GIS mapping and community survey will be used as the basis of community consultation.

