### Data analysis

Chi-squared analysis will be used to test for differences in the distributions of PA categories in the intervention and control areas. Multinomial logistic regression analysis will be used to derive odds ratios for the various physical activity categories between the areas. Qualitative analysis of the interviews and discussion groups will follow the principles of thematic analysis [30]. The interviews will be audio tape-recorded, transcribed and entered onto a database. Then using the qualitative analysis computer package N-Vivo it is planned to conduct a thorough coding of the data followed by identification of basic themes and larger themes.

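### Unequal selection weights are paired with a chi-squared test and multinomial regression without design-based variance; run in the ordinary way, the nominal 5% test rejects too often

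*Protocol article*

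**What the plan says.** **Weights.** Under Community survey, the protocol article draws a random sample of addresses and asks one adult at each to respond. Weighting is introduced for that reason: "Since only one person is being randomly selected at addresses which have more than one resident aged 16" or over, "at the analysis stage we would apply weights (equal to the inverse probability of selection) to adjust for this". The scaling of the weights is not stated.

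**Analysis.** Under Data analysis: "Chi-squared analysis will be used to test for differences in the distributions of PA categories in the intervention and control areas". The second method is regression: "Multinomial logistic regression analysis will be used to derive odds ratios for the various physical activity categories between the areas". Neither sentence mentions the weights or a variance method suited to them. Physical activity is the primary outcome, and the comparison is with the other wards of the city, using the Active People Survey.

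**Sample size.** Proposed sample size works from alpha .05 and power .8 and concludes: "we have calculated a required sample size of 283 participants at follow-up". No allowance for weighting appears there.

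**The concern.** An adult chosen as one of k at an address has selection probability 1/k and weight k. The weights therefore differ between respondents. They remove the bias towards people in small households, so weighted proportions are properly estimated.

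The difficulty is the standard error. An ordinary chi-squared test takes its sample size from the table total and assumes that each unit in the table is one independent person. With unequal weights that fails in two ways. If the weights are left as household sizes, a respondent from a three-adult address counts as three people. If they are rescaled to sum to the number of respondents, the total is right, but the extra variance from unequal weighting is still ignored. The same holds for ordinary standard errors from the multinomial model.

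This would happen even if residents were fully independent and everyone replied, so it is separate from ward clustering and non-response. At stake are the false-positive rate of the primary comparison and the stated precision of the effect size, which the Study aims section says will be used to design a larger controlled trial.

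**Working it through.** **1. The plan's own figure.** With the stated inputs ("Using Cohen's arcsine formula this gives a standardised effect size of 0.273", alpha .05, power .8), n per group = 2(1.960 + 0.842)² / 0.273² ≈ 211 two-sided, not 283. The article does not say whether 283 is per group or in total. That mismatch is a separate matter; 283 is used below only as the planned number of respondents.

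**2. Inputs.** From the article: weight = inverse selection probability within the address, 283 respondents, alpha .05, baseline proportion 7.5%. Assumed, because the article does not give it: the distribution of adults per responding address.

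**3. Formulas.** These take the weights as unrelated to the outcome, respondents as independent, and physical activity as two categories.
- Weights used as counts: inflation of the chi-squared statistic = E[w²] / E[w].
- Weights rescaled to sum to n: inflation = Kish factor = E[w²] / E[w]².
- True size of the nominal 5% test = 2[1 − Φ(1.96 / √inflation)].
- Effective n = 283 / Kish factor.

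**4. Results.**

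| Addresses with 1/2/3/4 adults (%) | E[w] | E[w²] | Inflation, counts | Size, counts | Kish factor | Size, rescaled | Effective n |
|---|---|---|---|---|---|---|---|
| 60/35/5/0 | 1.45 | 2.45 | 1.69 | 13.2% | 1.165 | 6.9% | 243 |
| 50/40/10/0 | 1.60 | 3.00 | 1.88 | 15.2% | 1.172 | 7.0% | 241 |
| 35/50/15/0 | 1.80 | 3.70 | 2.06 | 17.2% | 1.142 | 6.7% | 248 |
| 35/50/10/5 | 1.85 | 4.05 | 2.19 | 18.5% | 1.183 | 7.2% | 239 |
| 30/45/15/10 | 2.05 | 5.05 | 2.46 | 21.2% | 1.202 | 7.4% | 236 |

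Worked line (35/50/10/5): E[w] = 0.35 + 1.00 + 0.30 + 0.20 = 1.85 and E[w²] = 0.35 + 2.00 + 0.90 + 0.80 = 4.05. Inflation as counts = 4.05/1.85 = 2.19, and size = 2[1 − Φ(1.96/1.480)] = 18.5%.

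**5. Simulation.** Two weighted samples of 283, 7.5% active in both, 4,000 runs, for the second to fourth mixes. Rejection rates were 15.5%, 18.1% and 18.9% with weights as counts; 6.8%, 7.4% and 7.3% with weights rescaled; and 5.4%, 5.0% and 5.4% unweighted. The formulas are borne out.

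**6. Dependence on the comparator.** With household-size weights as counts in the intervention sample only, and similar assumed mixes, simulated rejection was 11.0-11.8% against an unweighted comparator of 500 and 15.0-18.2% against one of 5,000. Both comparator sizes are assumptions.

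**7. Intervals.** Uncorrected intervals have 1/√inflation of their correct width: 1/√1.69 = 0.77 down to 1/√2.46 = 0.64 with counts, and 1/√1.142 = 0.94 down to 1/√1.202 = 0.91 with rescaled weights.

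**8. Power.** If 283 is per group and h = 0.273, two-sided power is 90% unweighted and 84-86% at an effective n of 236-248. About 211 are needed for 80%.

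**The case against.** The best defence is that nothing stated is wrong. Inverse probability of selection is the standard design weight. The two analysis sentences name families of methods: a Rao-Scott test is a chi-squared analysis, and a pseudo-likelihood fit with robust errors is multinomial logistic regression. Scaling and variance estimation are details that an article may leave to a fuller document.

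Much of this stands. A reader might infer that weighted totals will simply replace the 283 respondents, so that an error rate in the teens is a property of the plan. The article does not say so; that result needs the weights to be entered as counts.

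A reader might also fold in the address sampling fraction. The study area is described as one "with an estimated population of ~10,000 adults", and 10,000/2830 = 3.53 would be the mean overall weight, giving error rates of 30% or more if used as counts. The text does not support this either, because the weights are introduced to adjust for choosing one adult within an address.

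What the defence does not remove is that the article itself fixes both the weights and the tests. Weighting followed by the ordinary form of either procedure overshoots under both scalings. Leaving the weights out of the test would keep its size but abandon the stated adjustment. Only a design-based form satisfies both sections, and none is named.

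**Conclusion.** The point holds in conditional form. If the stated weights are used with the named procedures as ordinarily run, the nominal 5% test rejects at about 7% with weights rescaled to n, and at about 13-21% with household sizes as counts. The first figure is the minimum consequence; the second depends on a use of the weights that the article neither states nor excludes.

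Both ranges rest on assumed household mixes (mean 1.45 to 2.05 adults per address) and on two groups weighted alike. The weighting of the Active People Survey data is not given, and step 6 shows that the count figure falls against a small unweighted comparator.

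A reader might also conclude that weighting defeats the stated power. It does not follow: an effective n of about 235-248 still exceeds the 211 needed for h = 0.273 if 283 is per group. The loss is a caveat on power, not a failure of it.

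**What to change.** - **Community survey:** keep the weights for the estimates, and state that they are sampling (probability) weights, not frequency counts.
- **Data analysis:** name a design-based (Rao-Scott) chi-squared test, and a weighted multinomial logistic model with robust (sandwich) standard errors.
- **Proposed sample size:** note that unequal weighting is expected to cost precision. A design effect of about 1.14-1.20, or an effective n of about 235-248 out of 283, is a working assumption to be replaced by the household sizes seen at wave 1.

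The cost is a few sentences and standard survey procedures, with no extra participants or data. The downside is somewhat wider intervals: about 7-10% wider than uncorrected ones with rescaled weights (√1.14 = 1.07 to √1.20 = 1.10).

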### Phase IV

#### Primary and secondary outcomes

##### Primary outcome measures

The primary outcome measure of effectiveness of this approach will be the change in physical activity in the three areas compared with the other wards in Stoke-on-Trent (using the Active People Survey [16]). The study is designed to detect a 10% increase (intervention areas vs. the rest of Stoke-on-Trent) in the proportion of participants reporting an increase in physical activity, made up of those initially engaging in some activity who increase this to the level recommended to derive health benefit and those initially doing little or no activity who increase to doing some regular activity. Objective measures of physical activity will be used for a random sub-sample of respondents to the community survey using 7-day accelerometry (ActiGraph) as a check on self-reported physical activity measures [26].

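### The accelerometer sub-sample of 300 does not fit the 283 survey respondents from whom it is to be drawn, on the protocol's own planning figures

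*Protocol article*

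**What the plan says.** Three places in the protocol article bear on this point.

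- **Size.** *Community survey*, under Phase 1, says that "a random sub-sample of 100 adults from each of the three Wards will be asked to wear an accelerometer" for seven consecutive days. The sentence presents this as additional to the survey.
- **Sampling frame and purpose.** *Primary outcome measures*, under Phase IV, says: "Objective measures of physical activity will be used for a random sub-sample of respondents to the community survey using 7-day accelerometry". The stated purpose is to check the self-reported activity measures.
- **Expected yield.** *Proposed sample size* says "we have calculated a required sample size of 283 participants at follow-up". It then assumes that 10% of surveys are returned and concludes that "the issued sample size will be 2830 surveys".

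*Community survey* adds that the wave-2 questionnaire, at 24 months, goes to the wave-1 respondents. No other number of expected respondents is given, and no allowance for loss between the waves.

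**The concern.** A random sub-sample has to be smaller than the set it is drawn from. Here the sub-sample has 300 members and the expected set has 283. The shortfall arises at invitation, before anyone declines to wear the device or returns unusable data.

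Accelerometry is the only objective check that the article names on a self-reported primary outcome. If the draw cannot be made at the stated size, field staff will have to improvise: approach every respondent, accept unequal numbers by ward, or look for wearers outside the survey. These choices produce different groups, and the protocol should settle which is meant.

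**Working it through.** **Inputs**

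- Wearers to be asked: 100 in each of 3 wards (*Community survey*).
- Frame: respondents to the community survey (*Primary outcome measures*).
- Surveys issued: 2830; assumed response: 10% (*Proposed sample size*).
- Wave 2 goes to wave-1 respondents only (*Community survey*).

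**1. The plan's own figure.** 283 / 0.10 = 2830 surveys issued. This reproduces, and so does the reverse: 2830 × 0.10 = 283 expected respondents.

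The 283 itself does not follow from the stated inputs. Cohen's formula is n per group = 2 × ((z for alpha + z for power) / h)². With h = 0.273, two-sided 0.05 and power 0.80 it gives 2 × ((1.960 + 0.842) / 0.273)² ≈ 211. With power 0.90 it gives 2 × ((1.960 + 1.282) / 0.273)² ≈ 282. That is a separate matter. The present check uses only the number issued and the response rate, as stated.

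**2. Sub-sample against frame**

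| | Sub-sample | Expected respondents | Difference |
|---|---|---|---|
| Total | 3 × 100 = 300 | 283 | 17 short |
| Per ward, equal split (assumed) | 100 | 283 / 3 = 94.3 | about 6 short |

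300 / 283 = 106%. The comparison of totals needs no assumption about the split: with 283 respondents over three wards, at least one ward must have fewer than 100.

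**3. Break-even.** To have 300 respondents to invite, the response must be at least 300 / 2830 = 10.6%, or at 10% the number issued must be 300 / 0.10 = 3000. Both need an equal split, and both use every respondent.

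**4. Chance variation.** Suppose that the true response is exactly 10%, returns are independent and about 943 surveys go to each ward (all assumptions). The binomial probability of 300 or more respondents in total is then about 15%, and of 100 or more in every ward about 2%.

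**5. If 283 must remain at wave 2.** Wave 1 must then supply 283 / retention. This exceeds 300 when retention is below 283 / 300 = 94%. At an assumed 80% retention, wave 1 needs 283 / 0.80 ≈ 354 respondents, hence about 354 / 0.10 = 3540 surveys, not 2830. Even then 300 is 300 / 354 = 85% of respondents.

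**The case against.** **The 283 is labelled as a follow-up number, so wave 1 could be larger.** This is the best counter-argument, since the accelerometer text stands in the baseline phase. It does not rescue the plan as written. The 10% is applied once, to the 2830 issued, which gives 283 at wave 1; wave 2 can only be the same or smaller. A larger wave 1 needs more surveys than the protocol states. It is true that adding an attrition allowance could remove the shortfall.

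**The wearers may be a separate sample of ward adults.** The *Community survey* sentence allows this reading, as it speaks of adults and not of respondents. *Primary outcome measures* names respondents. If a separate sample was meant, the two sections contradict each other and still have to be reconciled. Such adults could serve as a check only if they also completed the questionnaire, on which the article is silent.

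**The 2830 may be per ward.** That would be 8490 addresses in an area that *Study design* puts at roughly 10,000 adults, and the text gives 2830 as the issued sample as a whole.

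**The 10% is a planning assumption, not a ceiling.** This stands. A reader might infer that the draw is impossible. The documents do not support that: a response slightly above 10.6%, evenly spread, would make it arithmetically possible, although nearly as a census.

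**Consent and precision.** A reader might also infer that the mismatch makes the group self-selected, cuts it to 113 to 170 wearers, or costs precision. This does not follow. The 100 per ward is the number asked, so refusals would occur whatever the size of the frame. The range of 113 to 170 comes from applying an assumed consent of 40% to 60% to 283. The same rates applied to 300 give 120 to 180, so the mismatch itself accounts for about 7 to 10 wearers. The article states no precision or agreement target for the accelerometer data.

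**Conclusion.** The point holds as an inconsistency between three stated figures: 300 to be asked, a frame restricted to survey respondents, and 283 expected respondents. On those figures the group falls 17 short even if everyone is approached, and it would not be a random sub-sample. The total rests only on the protocol's 2830 and 10%; the figure of about 94 per ward also assumes an equal split.

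The consequence is modest. It concerns the size and description of the objective check on self-report. Nothing in the article makes the primary comparison or its sample size depend on the accelerometer data, so the mismatch should not be read as a fault in the main test.

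**What to change.** Reconcile *Proposed sample size*, *Community survey* and *Primary outcome measures* in one of two ways:

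1. Invite all wave-1 respondents to wear the device, and drop the description as a random 100 per ward; or
2. Keep a random sub-sample and restate the per-ward number as one that the expected respondents (about 94 per ward if split equally) can supply, with room left for a random draw.

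In either case, state in *Community survey* that wearers are drawn from survey respondents, as *Primary outcome measures* already says. If the number issued is revised, for example to allow for loss by wave 2, recompute the sub-sample from the new expected yield. Issuing 3000 surveys (170 more) would close the gap in numbers at a 10% response, but it would still be a census and not a random draw.

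The cost is wording and a slightly smaller stated sub-sample: at most 283 invited instead of 300 under the first option, fewer under the second.

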### Phase II: Establish working Groups for intervention planning

Each ward of Stoke-on-Trent, UK has an Area Implementation Team (AIT) which is directly aligned to Stoke-on-Trent City Council, Stoke Primary Care Trust, and the Local Strategic Partnership and involves membership from joint services (e.g. Health, Police and Fire Services, private, community and voluntary sector organisations). The aim here is to bring both the target community and a multidisciplinary professional perspective to the process of planning the intervention. Encouraging individuals and groups for whom the intervention is intended will help optimise sustainable consensus and action. This will be achieved through the AIT network by the formation of neighbourhood "Working Groups" with representation from those who are the intended beneficiaries and those implementing the programme taking account of the need for culturally relevant programmes for diverse groups. Community participants are likely to be a mixture of unaffiliated residents, voluntary organizations, staff members from the AIT and leaders from community organizations. It is recognized that over time membership of these groups may change. The task of these groups will be to help determine performance objectives and determinants to develop an overall matrix of change objective grid; this process is described in Phase III. The AIT Network will help with the setting up and coordination of these groups and a dedicated Community Development Worker (CDW) will be allocated to each area. These CDWs will act as agents and catalysts for change and will work across several levels and will be responsible for increasing motivation and demand for health. This will be achieved through an approach which combines community engagement with supportive policy change that focuses on facilitating and creating healthy urban environments (as identified by community members themselves).

